### General Study Design

The ENIGMA-Vis is designed to be a randomized, double-blind, and placebo-controlled three-period trial (RBR-46tjy3) to investigate the effects of nicotine gum administration on vision. The diagram is shown in Table 1. This trial comprises three main gum administrations (placebo, 2-mg, and 4-mg doses). Participants will be followed up at 4 weeks, and the assessments will be performed in week 0 (baseline) to week 3. Female participants will be tested outside their luteal phase.

**TABLE 1 T1:** Measures by timepoint for the schedule of enrolment, interventions, and assessments.

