#### Blinding/Masking

The study coordinator will generate the allocation sequence, and two researchers will administer the nicotine gum, but they will be blind with regard to the dosage. Two different researchers will conduct the statistical analyses. They will be unaware of the condition analyzed. The participants will be interviewed at the end of the study (by the selected researchers) to determine if the blinding was broken. If the blind is broken, additional analyses without the unblinded cases will be conducted to test the effects of unblinding. Some participants might be able to tell which dose they received on the basis of physical alterations; however, malaise will be assessed at the end of each period session.

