### Sample Size

There were no previous reports of sample size estimation from a meta-analysis or equivalent study. Because of the lack of this information, the effect size will be estimated using the minimal meaningful effect size (0.05) (Sullivan and Feinn, 2012) and the power will be used considering a common value in clinical trials (Charan and Biswas, 2013). Considering a two-sided test with an alpha value of 0.01 (or 0.02 for a one-sided test) and a power of 85% (or 0.85), the sample size would require at least 42 individuals to complete the three periods for each study. As this trial is a single group model, with an anticipated 20% attrition rate, our main intention is to enroll 50 individuals for each study (Study 1, *N* = 50; Study 2, *N* = 50). Although our sample size is larger than that of previous studies using these tests (Andrade et al., 2019; Fernandes et al., 2019a,b), it is important to provide an estimation that covers our outcomes (e.g., BMIs and cotinine).

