#### Additional Analyses

Missing data will be considered as random (MAR), and the maximum likelihood estimation (MLE) will be used. Under the MAR assumption, MLE appears to represent an interesting and unbiased approach, even to continuous and discrete variables (Dziura et al., 2013). Nevertheless, we will analyze individuals with missing data and without missing data. We expect to have no more than 5% of missing data and differences between with and without missing data.

Exploratory analysis to investigate whether sex, age, and level of education are predictors of response will be performed. Multivariate regression analysis will be used to investigate whether demographics would be predictors of the effects of nicotine gum. We will also conduct a separate regression analysis to investigate whether or not cotinine serum levels would be predictors of visual performance. These variables can be also used as mediators of the interaction between conditions.

Finally, adverse events will be presented as percentages in each condition. Cochran’s *Q* test will be conducted to investigate the effectiveness of the masking and blinding (on this analysis, we will calculate the ratio between errors and correct responses regarding the condition in which the participant believed was applied).

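### Cochran's Q compares correct-guess rates between conditions, not with chance, so it cannot by itself show whether the blind held

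*Protocol article*

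**What the plan says.** Each participant receives all three gums, and the article fixes both the test of blinding and the data for it. Under Additional Analyses, a Cochran's Q "test will be conducted to investigate the effectiveness of the masking and blinding", and for this "we will calculate the ratio between errors and correct responses regarding the condition in which the participant believed was applied". No comparison with a chance rate is stated there or under Blinding/Masking.

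The Blinding/Masking section gives the source and the use of the guesses: "The participants will be interviewed at the end of the study (by the selected researchers) to determine if the blinding was broken". It then says: "If the blind is broken, additional analyses without the unblinded cases will be conducted to test the effects of unblinding". It also concedes the likely route of unblinding: "Some participants might be able to tell which dose they received on the basis of physical alterations".

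**The concern.** A blind holds when guesses are unrelated to the gum received. The null hypothesis of Cochran's Q is a different one: that the proportion of correct guesses is equal across the three conditions. The two can part in both directions.

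- If participants recognise all three gums equally well, the proportions are equal and Q has nothing to find. A non-significant result would naturally be reported as successful masking.
- If participants cannot tell the gums apart but tend to give one answer, that answer is right more often in its own condition. The proportions then differ, and Q can be significant although the blind is intact.

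This matters because the main hypothesis is directional (better vision at higher doses), the outcomes are thresholds derived from participants' own responses, and the article expects that some participants may recognise the dose. Q is the only formal test of blinding that the article names, and further analyses follow if the blind is judged broken.

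**Working it through.** The article gives no figure for the blinding check, so there is none to reproduce.

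**Inputs.** k = 3 conditions (General Study Design). n = 42 completers per study (Sample Size: "the sample size would require at least 42 individuals to complete the three periods for each study"). No significance level is given for this test; 0.05 is assumed. One guess per session, scored right or wrong, is assumed. The article has no guessing data, so all guess probabilities below are assumptions, shown as a range.

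**Formula.** C_j is the number correct in condition j, R_i the number correct for participant i, and N the total correct:

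Q = (k−1)[k ΣC_j² − N²] / [kN − ΣR_i²], referred to chi-square on k−1 = 2 degrees of freedom.

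**Two extremes by hand, n = 42.**

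- All guesses correct: C = (42, 42, 42), N = 126, every R_i = 3. Numerator 2 × (3 × 5,292 − 15,876) = 0. Denominator 378 − 378 = 0. Q = 0/0, undefined.
- Everyone always answers placebo, so guesses carry no information: C = (42, 0, 0), N = 42, every R_i = 1. Numerator 2 × (5,292 − 1,764) = 7,056. Denominator 126 − 42 = 84. Q = 84, p about 6 × 10⁻¹⁹.

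**Between the extremes.** Simulated rejection rates of Q, n = 42, 5% level, at least 20,000 trials per row:

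| Situation | Q rejects |
|---|---|
| Blind broken, 95% correct in every condition | 4.4% |
| Blind broken, 90% correct in every condition | 4.8% |
| Blind broken, 80% correct in every condition | about 5% |
| Blind broken, 70% correct in every condition | 5.0% |
| Blind intact, no preferred answer | 4.8% |
| Blind intact, the three conditions guessed in random order | 5.0% |
| Blind intact, answers 40/30/30 | 15.6% |
| Blind intact, answers 50/30/20 | about 76% |
| Blind intact, answers 60/25/15 | about 99% |
| Unequal unblinding, correct 33%/33%/80% | 99.8% |

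**A comparison with chance.** Let T be a participant's number of correct guesses over the three sessions. If guesses are unrelated to condition, with answer probabilities a, b and c, then E(T) = a + b + c = 1 whatever the preference. A one-sided, one-sample test of mean T against 1 (n = 42, 5% level) rejects in about 4% of trials when the blind is intact, with or without a preference, and in 3.2% under random-order guessing. It rejects in 98% at 50% correct in every condition and in essentially 100% at 80%. It separates the cases that Q confuses.

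**Leaving out unblinded cases.** The loss by chance alone, with an intact blind, depends on what counts as a case:

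- At least one correct of three: 1 − (2/3)³ = 19/27 = 70.4% for independent guesses, or 4/6 = 66.7% for random-order guesses. That is about 28 to 30 of 42.
- All three correct: 1/27 = 3.7%, or 1/6 = 16.7%. That is about 2 to 7 of 42.

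**The case against.** The strongest defence is that unblinding through physical effects would probably differ by dose, and Q does react to unequal accuracy. Besides the 99.8% above, it rejects in 86% of trials for correct rates of 50/50/80%, and in 81% if half the participants truly recognise 4 mg and otherwise guess in random order. This stands, and it means Q is not useless. But its power falls as accuracies converge (47% for 70/50/70%), and a significant Q still cannot be told apart from a preferred answer.

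Second, the plan does not rest on the p-value alone. The ratio of errors to correct answers would show zero errors if everyone guessed right, and Q would then be undefined, not reassuring. This also stands. The ratio, however, has no stated chance benchmark for anything short of that extreme.

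Third, a reader might infer that Q generally flags an intact blind. It does so only when answers favour one condition; otherwise it keeps its nominal level.

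Fourth, a reader might infer that the follow-up analysis would discard most participants by chance. The article does not support this. It does not say that one correct guess makes someone an unblinded case, and that definition may properly be left to the full protocol. The 67–70% is one end of a range whose other end is 4–17%. The exclusion is also an additional analysis that leaves the primary one intact.

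**Conclusion.** The concern holds in a limited form. Cochran's Q does not answer the question that the article sets for it. It stays at about its 5% level when the blind is broken equally in all conditions, and it can reach 76–99% with an intact blind and a marked answer preference. These sizes rest on assumed guess probabilities, 42 completers and a 5% level; the mismatch between the hypothesis tested and the purpose stated rests on none of them.

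The analysis without unblinded cases is acceptable only as a sensitivity analysis. A correct guess mixes luck with effects felt after dosing, so removing correct guessers selects on a response to treatment. No primary result changes.

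**What to change.** Replace Cochran's Q as the test of blinding with the mean number of correct guesses per participant against 1, with a confidence interval. Show beside it the full table of guesses by condition, or per-condition blinding indices read jointly. Require a forced choice, or state how a 'don't know' answer is handled, because the expectation of 1 assumes that every session yields one of the three answers. If every participant is right every time, T has no variance; the mean of 3 then speaks for itself.

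Two obvious alternatives are weaker. Separate tests of each condition's proportion against 1/3 also flag an intact blind with a preferred answer: at least one rejects in 74% of trials for 50/30/20 and in 98% for 60/25/15. Adding the guessed condition to the outcome model conditions on a post-dose variable and coincides with treatment when all guesses are right. The article plans MANOVA, so it would also need a new model.

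Label the analysis without unblinded cases as a sensitivity analysis, and fix before unblinding what counts as a case. The cost is a change of test in an auxiliary analysis and a sentence or two of text.

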## Discussion

ENIGMA-Vis aims to investigate short-term effects of nicotine gum on vision in a population of healthy non-smokers. The findings obtained here will allow us to undertake the controlled investigation of nicotine effects on vision. We believe that this study design, altogether with the use of reliable tools such Metropsis software (CSF) and the CCT, will additionally allow us to observe the acute (short-term) effects of the nicotine. As follows, we can address an important but understudied area: the role of nicotine on vision. With this trial, we intend to open new avenues on visual research. Caution should be taken with the generalization of our findings, however.

### Anticipated Results

We expect, based on our hypothesis, that nicotine could lead to an improvement in visual processing, with the higher dose producing the largest improvement.

As observed in our past studies (de Almeida et al., 2018; Fernandes et al., 2018b,c; Silva et al., 2020), tobacco addiction resulted in early-stage visual processing impairments. However, smoking comes in the form of (i) smoke absorption and (ii) the consumption of numerous health-damaging compounds (nicotine is one of the numerous existing components) (Silva et al., 2020). In the mammalian brain, nAChR isoforms are expressed on mesolimbic and nigrostriatal neurons. Because about one-fourth of the brain is involved in visual processing and neurotransmitters such dopamine, GABA, and glutamate are also involved, it is not hard to explain that transient nicotine administration can have effects on vision (Balfour and Munafò, 2015). Note that the expression of nAChRs in the brain does not imply agreement of intakes = effects. This may be explained because the intake of nicotine gum is relative to the maximum amount and other factors such peak concentration, age, BMI, and gene expression (Benowitz, 2010; Balfour and Munafò, 2015). In light of these factors, our attempt is to control confounding factors and investigate the extent to which nicotine can improve vision.

### Strengths and Limitations of This Trial

We have proposed a different approach, and this research is a first step toward a more profound understanding of the effects of nicotine on vision. To our knowledge, this is the first trial attempting to investigate it. We must mention that this study still cannot be placed as a final step of the investigations of visual processing, and because of this, we cannot simply state that our findings should be labeled as the last step of investigations using nicotine gum on vision. We need, first, to investigate visual processing in terms of contrast sensitivity and chromatic contrast discrimination using stimuli, which could involve all the three visual pathways. Visual processing may be a door to cognition. Understanding the improvements may help promote policies that seek to act directly for individuals with impairments in visual processing before these impairments progress to higher-order cognition (Butler et al., 2005; Tacca, 2011).

The strengths of this study include having a rigorous controlled clinical trial with a larger sample size. Also, the use of reliable tools for investigating visual processing can be argued as a strength of this research. Nevertheless, some concerns regarding our study design should be underscored. First, although the sample size is larger than used in previous studies, we do not have a solid base to conclude that it is a sufficiently large sample size. Second, due to the high cost, we will not be able to provide an extensive pharmacological and physiological explanation of the results. This is particularly the case for the measuring the cotinine levels. It may be too costly to obtain cotinine levels for all participants (*n* = 100), and so these levels will be based on randomly selecting (see section “Baseline Measures”). Third, because fixation is not controlled and eye movements are not monitored, it is unknown as to whether any differences in search patterns after ingesting nicotine would be related to any differences in the sensitivity. However, studies showing that practice has minimum effects on these two tests suggest that changes in search patterns would not affect sensitivity (Costa et al., 2006; Fernandes et al., 2019a, 2020). Any search patterns would be relatively simple, shifting one’s gaze horizontally for the CSF and both horizontally and vertically for the CCT. Previous findings on eye movements indicate that saccadic latencies are shorter after ingesting nicotine, and so any improvement in saccadic eye movements would likely be reflected in their response times rather than in their sensitivity (Bowling and Donnelly, 2010). Although the total time to complete the CSF and the CCT is different (e.g., 15–20 and 12 min, respectively), both tests will be completed within the time for the average peak concentration of nicotine (< 45 min).

Given these limitations, our trial will be an initial, but important, investigation about the effects of nicotine on vision.

In summary, we believe that our results will provide motivation for follow-up studies. Our results may also help understand why certain groups (e.g., people with schizophrenia) demonstrate both visual dysfunctions and elevated rates of tobacco addiction.

## Ethics Statement

The studies involving human participants were reviewed and approved by Ethics in Research of the Health Sciences Center of Federal University of Paraiba (Trial register number: RBR-46tjy3). Written informed consent was not provided because subjects have not yet been recruited. Written informed consent will be obtained from all of the participants indicating that they had been informed of all aspects of the trial at the beginning of the trial.
